### Participant timeline {13}

SPIRIT schedule of enrolment, intervention, and assessments.

Participant timeline is outlined in Fig. 2.

Eligibility (T0): Parents of young children may complete the eligibility screener to determine whether they are eligible for participation in the BEAM program.

Week 0 (T1): Eligible participants who consent to participate in the program will receive notice of enrolment. Participants will be fully enrolled in the program after they participate in an orientation meeting with their peer coach and/or a member of the research team and complete the pre-test assessments, including primary, secondary, and exploratory outcome measures.

Week 1: Participants will receive an email regarding BEAM app access login and account information. Program information will be sent electronically to participants from the study team.

Weeks 2–13: Participants will watch weekly videos and will complete symptom tracking questions for self-monitoring purposes. Participants will begin engaging in the forum and will also participate in check ins with their peer coach, continue engaging in the forum, and connect with the Systems Navigator as needed.

Weeks 13–16 (post, T2): Participants will complete a full post-test assessment of primary, secondary, and exploratory outcome measures.

Month 5–7 (follow-up, T3): Participants will complete a follow-up assessment of primary and secondary outcome measures.

Month 11–13 (follow-up, T4): Participants will complete a follow-up assessment of primary and secondary outcome measures.

### Sample Size

In total, we aim for *N* = 400 participants to participate in the BEAM program over two years. However, we may modify or extend eligibility based on participant attrition rates and budgetary capacity. Sample size was determined based on data from our telehealth pilot in preschoolers and related effectiveness trials comparing evidence-based practices to services as usual in treatment seeking families [68]. We assume that participation in BEAM will evidence moderate reductions in parent mental health, based on prior evidence from previous BEAM trials. For this effectiveness trial, we anticipate the effect size may be approximately 25% smaller than in trials delivered directly by our practitioner team. The sample size calculation was conducted to ensure adequate power to detect this reduced effect size. Specifically, we conducted a power analysis assuming a type I error rate (α) of 0.05 and a power (1-β) of 0.80, which corresponds to a 80% probability of detecting a statistically significant effect if it exists. The calculation was based on a linear mixed-effects model, which accounts for repeated measures over time. To account for potential loss to follow-up, we conservatively assumed an attrition rate of 30%.

With these parameters, we determined that a sample size of N = 400 participants would provide sufficient power to detect the expected effect size while maintaining robustness against attrition and variability in outcomes. This calculation ensures the trial is appropriately powered for the primary analysis of intervention effectiveness.

### Recruitment

Recruitment will involve a multi-faceted approach, encompassing four primary recruitment streams. First, we will collaborate closely with Manitoba’s Shared Health Crisis Response Services, including programs offering crisis assessment and post-crisis intervention to individuals across the province, to engage front-line staff in the recruitment process. Front line staff will receive training to enhance their familiarity with BEAM as a resource. The training will include comprehensive insights into BEAM program specifics, eligibility criteria, as well as introduce staff to our BEAM Systems Navigator and the stepped care model. Secondly, we will target recruitment efforts at primary care offices and provincial health services (e.g,. Shared Health Mental Health Services), in consultation with the Manitoba Pediatric Society and Doctors Manitoba. Recruitment through this stream will utilize light touch strategies such as poster and pamphlet drop-offs to sites. The third recruitment avenue involves collaborating with various community organizations, child care centres, and family resource centres (e.g., Family Dynamics, United Way Winnipeg, Acorn Family Place). Through these partnerships, we aim to expand the reach of our recruitment efforts and ensure that families from diverse backgrounds are included in the trial. Finally, our online recruitment efforts will include sharing posters and short video advertisements on social media platforms (e.g., Facebook, Instagram). Through these various approaches, we aim to facilitate comprehensive recruitment and maximize the representativeness of the trial.

Participant screening and recruitment will be done on a continuous, rolling basis over two years, from December 2023 to September 2025.

### Assignment of interventions: allocation

Not applicable, there will be no assignment to different interventions.

### Assignment of interventions: blinding

Not applicable.

## Data collection and management

### Plans for assessment and collection of outcomes {18a}

Data will be collected via self-report measures, the use of back-end app engagement data, forum content, peer coach and system navigator meeting attendance, and administrative data. Primary outcomes, secondary outcomes, and exploratory outcomes are outlined in Table 1. There will additionally be measures of participant *sociodemographic information*, *service utilization*, *food insecurity*, and *housing instability*. These constructs will be assessed using questionnaires designed for BEAM and a questionnaire from the Canadian Community Health Survey to enable comparison of BEAM participant experiences with food insecurity to those of the Canadian population average. Peer coach check-in attendance, system navigator meeting attendance, and app analytics will be used to track program engagement and adherence. The content of posts and comments within the forum will be used for program improvement purposes. Administrative data records will be drawn from the Manitoba Population Research Data Repository, maintained by the Manitoba Centre for Health Policy (MCHP). All analyses will be completed by MCHP analysts and no person-level administrative data will be accessible to our research team.

### Plans to promote participant retention and complete follow-up {18b}

Study-related reminders will be sent to participants when self-report questionnaires are being collected (T1-T4). Eligible participants will receive up to a total of $200 Canadian (CAD) in compensation for participating for the entire duration of the study, see Table 4. Participants will receive an honorarium of $10 CAD for completing the pre-assessment questionnaires, $30 CAD for completing the post-intervention assessment, $40 CAD for completing each follow-up assessment, and $10 CAD at each timepoint to complete a school readiness questionnaire. Participants will receive an additional $10 at post and follow-up timepoints if they complete the questionnaires within 2 weeks. Additionally, participants will receive $10 CAD if they complete half of all weekly surveys (6 or more of the 12 surveys). Furthermore, the clinical and research team will have weekly meetings to monitor the adherence and retention of participants. For instance, participant engagement will be discussed and additional email check-ins with participants will be performed when advised by the registered psychologists on the team.

**Table 4 Tab4:** BEAM Program Participant Compensation

	Pre-program (T1)	Post-program (T2)	6 mo. follow-up (T3)	12-mo follow-up (T4)	Total
45-min questionnaire	$10	$30	$40	$40	$120
15-min school readiness questionnaire	$10	$10	$10	$10	$40
Complete questionnaires within 2 weeks		$10	$10	$10	$30
Complete at least 6 of 12 weekly in-app surveys	$10				$10
					**$200**

### Data management {19}

REDCap is managed by The George and Fay Yee Centre for Healthcare Innovation, which is a hired consultant on the proposed project and will support secure data collection and management. Data will be stored on a secure server in accordance with the University of Calgary's Data Retention Policy and the University of Manitoba's PHIA policies. Once data is downloaded, all identifying information will be removed, which aligns with the University of Manitoba's REDCap policies. All patient health information will be kept for up to 5 years. Birth dates will be converted into age in months, and birthdate information will then be destroyed. Measures to promote the quality of data entry will include range checks for all data values entered and having three research assistants review and ensure correct data entry in REDCap.

### Confidentiality {27}

The BEAM program will occur on a secure online platform and participant confidentiality will be protected throughout all phases of the study in accordance with University of Manitoba ethics guidelines. All questionnaire data will be stored securely on REDCap or on password-protected University of Manitoba secure data servers. Precautions will be taken to manage any risks to confidentiality. These precautions include a Risk Management Protocol, Data Management Protocol, and participant agreed upon Terms of Use. During the group drop-ins, participant anonymity cannot be guaranteed. These sessions will be hosted on a secure Zoom for Healthcare account and will be password-protected. The peer coaches will outline the limitations of confidentiality and anonymity at the beginning of each drop-in session. Drop-in sessions will not be recorded or included in any assessment; however, attendance will be tracked. Participants will become familiar with the limitations to confidentiality and of the measures that will be taken to protect the confidentiality during the informed consent process before beginning in the study.

### Plans for collection, laboratory evaluation, and storage of biological specimens for genetic or molecular analysis in this trial/future use {33}

Not applicable, no biological specimens will be collected.

## Statistical methods

### Statistical methods for primary and secondary outcomes {20a}

Analysis of the primary outcome (parent mental health symptom composite) will examine change across all four timepoints: pre-intervention (T1), post-intervention (T2), 6-month follow-up (T3), and 12-month follow-up (T4). A two-level linear mixed effects model with random slopes will evaluate the hypothesis that parent mental health symptoms will evidence significant reductions from T1 to T2, T1 to T3, and T1 to T4. This model will account for sociodemographic and socioeconomic factors as well as other theoretically- and empirically-motivated covariates [69]. Baseline mental health symptom severity (T0) will be examined as a baseline moderator. Other theoretically- and empirically motivated exploratory baseline moderators of change may also be examined. The same two-level linear mixed effects modelling approach will evaluate change in secondary outcomes (i.e., individual parent mental health symptoms, parenting behaviours, child mental health and development). All data will be included following an intention-to-treat approach, where missing data will be handled using full information maximum likelihood estimation. Sensitivity analyses will be used to examine complete-case methods should the assumption of missing at random be met. Analyses will be led by the research team, in consultation with the Centre for Healthcare Innovation, using MPlus v8.0. The research team will also investigate if there is baseline (T0) moderation by symptom severity to examine whether the BEAM intervention is more effective for participants who have higher symptom levels before receiving the intervention (e.g., depression, anxiety, anger, sleep disturbances).

To measure the impact of BEAM via implementation metrics and cost-effectiveness we will use benchmark uptake and attrition markers, to determine the extent to which the BEAM program succeeds on key implementation metrics including acceptability, feasibility, fidelity, cost, and sustainability [70]. Mixed-methods data from agency perspective, app usage, and user experience will inform continuous improvements using implementation metrics we have used in the past including app, group and coach engagement as well as user satisfaction. Quantitative data related to app usage and UX data will be linked to outcome variables to elucidate what components of program engagement are associated with symptom remission.

Analysis of administrative-linked outcomes will enable comparisons between BEAM families and those families in ‘population-average’ and ‘risk-matched’ control cohorts drawn from MCHP’s provincial administrative database. While the ‘population-average’ control cohort will be comprised of parents who match the basic demographics of BEAM participants and their children (e.g., age, number of children), the ‘risk-matched’ control cohort will consist of parents of young children who match the demographics, physical health, mental health, child developmental, and service utilization characteristics of BEAM participants and their children. This will be accomplished in consultation with MCHP by matching Manitoban families in the administrative database to BEAM families on these risk factors. These matching criteria will be developed using MCHP’s high-dimensional propensity scores matching algorithm (hdPSs) which, across multiple algorithmic iterations, identifies risk factors that are correlated with the features of the participants who have enrolled in the BEAM program [71]. This data-driven propensity score development strategy is commonly used and will allow our team to match BEAM participant risk to non-BEAM participants in the community. Comparing trajectories in health and social outcomes between BEAM participants, ‘risk-matched’ controls, and ‘population-average’ controls will generate knowledge about the extent to which children experience stable, cumulative, or “sleeper” (i.e., not observable until after developmental time periods) benefits over time. If we find children experience diminishing effects such that program benefits are only present in the first year, this may indicate that further intervention is required to sustain program achievements. All administrative-linked analyses will be conducted by MCHP statisticians.

Exploratory qualitative data will be analyzed thematically [38]. First, two coders will analyze the data concurrently, but independently read the transcripts for surface descriptive content, and organize like-with-like ideas. Second, transcripts will be re-read for latent meaning to better understand participants'meaning, including looking for contradictory or confirmatory statements. Each coder will independently generate and systematically apply themes across all transcripts. Semantic validity checks will ensure different words and phrases within a category have similar meanings [38]. To further enhance rigor, constructs will be deemed saturated (akin to statistical significance in quantitative work) when no new or additional constructs are identified, consensus is reached on all overarching themes, and no alternative explanations were found with subsequent interviews [38].

Exploratory health economic analyses will examine BEAM’s delivery cost per QALY and will compare cost per QALY to that of extant mental health programming [36, 37]. This analysis will be conducted in consultation with health economist and trial steering committee member ([name]).

### Interim analyses {21b}

No interim analyses are planned.

### Methods for additional analyses (e.g., subgroup analyses) {20b}

Subgroup analyses may be explored based on emergent research questions of interest.

## Methods in analysis to handle protocol non-adherence and any statistical methods to handle missing data {20c}

Analyses will be conducted on an intent-to-treat (ITT) basis [72]. Regardless of participant attrition or withdrawal, data for every participant to the point of attrition will be included in ITT analyses. Missing data will be handled using maximum likelihood [73], which estimates values based on all available data and will produce unbiased model parameters given that the data are independently and identically distributed [74]. Sensitivity analyses will be used to examine complete-case methods should the assumption of missing at random be met.

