**Methods:**

A single arm trial with repeated measures will be used to evaluate the effectiveness of implementing the BEAM intervention in the community with a sample of 400 parent participants with a child aged 24–71 months. Participants must self-report moderate to severe symptoms of depression, anxiety, parenting stress, and/or anger at time of enrolment (T0) and live in the province of Manitoba, Canada. Individuals will be recruited through four streams including the (1) Manitoba Crisis Response Services, (2) primary care offices (paediatricians and/or general practitioners), (3) Manitoba family community organizations and child care centres, and (4) social media. Study participants will complete 12 weeks of psychoeducation modules, with access to an online social support forum and check ins with a peer coach. Assessments of parent and child mental health symptoms will occur at pre-test before BEAM begins (T1), immediately after the last week of the BEAM intervention (post-test, T2), 6-month follow-up (T3), and 12-month follow-up (T4).

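### The only stated missing-data sensitivity analysis, complete-case, is made conditional on missing at random, which is when it is least useful

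*Protocol article*

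**What the plan says.** The primary analysis, in section {20a}, is a two-level linear mixed model with random slopes for the parent mental health composite. Its contrasts are T1 to T2, T1 to T3 and T1 to T4, on an intention-to-treat basis, with full information maximum likelihood for missing data.

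One missing-data sensitivity analysis is stated, in the same words in {20a} and {20c}: "Sensitivity analyses will be used to examine complete-case methods should the assumption of missing at random be met".

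Section {20c} justifies maximum likelihood as a method "which estimates values based on all available data and will produce unbiased model parameters given that the data are independently and identically distributed".

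Two other statements bear on the point. The abstract describes the design: "A single arm trial with repeated measures will be used to evaluate the effectiveness". The Sample Size section says of attrition: "To account for potential loss to follow-up, we conservatively assumed an attrition rate of 30" per cent.

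**The concern.** A sensitivity analysis should ask what happens to the result if the assumption behind the primary analysis fails. Here that assumption is missing at random (MAR), and the check is scheduled only if the assumption holds. The check is therefore withheld in the situation that would put the primary result in doubt.

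The justification in {20c} adds to the problem. Independent, identically distributed participants whose dropout depends on their unobserved outcomes still give biased maximum likelihood estimates. The condition that matters is MAR with a correctly specified model, and {20c} does not attach it to the claim of unbiasedness.

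The effect estimate in this trial is within-person change. If parents who are doing worse leave more often, which is plausible though not shown, the estimated improvement from T1 is too large. The primary analysis has no concurrent comparison that could expose or partly offset this.

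**Working it through.** **1. The rule, case by case**

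| If dropout is | Primary maximum likelihood | Complete-case | Does the stated rule run complete-case? |
|---|---|---|---|
| Completely at random | valid | valid, less precise | yes (a special case of MAR) |
| At random, depending on observed scores | valid with a correct model | generally biased | yes |
| Not at random | biased | generally biased | no |

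Complete-case analysis can also be valid when dropout depends only on covariates in the model. In no row does it tell the reader whether the primary result survives informative dropout. The trigger also cannot be operated, because observed data do not distinguish MAR from missing not at random.

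Two kinder readings do not rescue the sentence. If 'met' was meant to be 'not met', complete-case analysis still does not address informative dropout. If 'completely at random' was meant, the check is valid but compares two analyses that are both already sound.

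**2. Numerical check of step 1**

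This is a large-sample simulation with assumed settings, none of them from the protocol: 200,000 participants, four visits, SD 1, correlation 0.5 between visits, 30% cumulative monotone dropout, and dropout log-odds rising by 1 per SD of the previous score (MAR) or the current score (not at random). The true T1-to-T4 change is -0.375 SD.

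| Dropout | Maximum likelihood | Complete-case | Gap |
|---|---|---|---|
| Completely at random | -0.37 | -0.37 | 0.00 |
| At random | -0.37 | -0.31 | 0.06 |
| Not at random | -0.48 | -0.42 | 0.06 |

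The gap between the two methods is about the same when maximum likelihood is right as when it overstates the benefit by about 0.1 SD (0.48 - 0.375 = 0.105). Under these settings the comparison could not reveal the problem even if it were always run.

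**3. Size of the exposure**

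Inputs:
- Planned N = 400 and attrition 30% (Sample Size), so 400 x 0.70 = 280 completers.
- Retention of 84% in the earlier phase II RCT (Introduction, section on the BEAM program), so 16% loss.
- Completer mean change c = 0.375 SD. This is an assumption: Sample Size says only that the reductions are moderate and that "we anticipate the effect size may be approximately 25% smaller than in trials delivered directly by our practitioner team". Taking moderate as 0.5 gives 0.5 x 0.75 = 0.375. No numeric effect size is stated, so N = 400 itself cannot be reproduced.

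With dropout fraction p and mean improvement m among dropouts, overall change = (1 - p) x c + p x m.

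| | 16% loss | 30% loss |
|---|---|---|
| Dropouts unchanged (m = 0) | 0.84 x 0.375 = 0.315 SD | 0.70 x 0.375 = 0.2625 SD |
| Reduction relative to completers | 16% | 30% |
| Worsening among dropouts that brings the overall change to zero, (1 - p) x c / p | 0.315 / 0.16 = 1.97 SD | 0.2625 / 0.30 = 0.875 SD |

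Here c must be the completers' mean. A maximum likelihood estimate under MAR already refers to all enrolled participants, so multiplying it by 0.70 would be wrong. The formula also gives all dropouts one mean change at the visit in question. Parents lost later still contribute earlier data under the plan, which the formula ignores.

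**The case against.** The primary analysis is standard: maximum likelihood on all available data, by intention to treat. Nothing here shows it to be the wrong choice. The article condenses a fuller protocol, and the statistical analysis plan is not shown. An analysis under missing not at random is commonly specified there. A reader might infer that the trial has no check on informative dropout at all; the document does not support that, since such a check may exist elsewhere. What stands is narrower: the rule and the validity condition that this document does state are wrong as written, and the rule appears twice.

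A reader might also infer that the independence clause in {20c} overlooks the correlation between visits of the same parent. It need not. The two-level model in {20a} handles that correlation, and the clause can be read as independence between participants. The fault is that it names the wrong condition for missing data.

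Thirty per cent is the protocol's own conservative planning figure, it is not assigned to a particular visit, and the earlier RCT lost 16%. The illustration therefore has to cover both. Across that range, under the assumed 0.375 SD, dropouts who stay at their T1 level reduce the improvement but do not remove it.

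Finally, a control arm would cancel dropout bias only if dropout worked alike in both arms. The single-arm design means the bias enters directly; it does not follow that a controlled design would have been free of it.

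**Conclusion.** The point holds in this limited form. The condition on the complete-case analysis in {20a} and {20c} is inverted and cannot be operated, complete-case analysis would not address informative dropout even without the condition, and {20c} names the wrong assumption for unbiasedness.

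If completers improve by 0.375 SD and dropouts stay at their T1 level, the overall improvement is between 0.315 SD (16% loss) and 0.26 SD (30% loss). To reach zero, dropouts would have to worsen by about 1.97 SD or 0.875 SD respectively. These figures rest on the assumed completer change and on one common mean change among dropouts. The direction rests on parents who do worse leaving more often. The true dropout mechanism is unknown, so neither these figures nor the simulation predicts the bias.

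This should be fixed, but it is a flawed sensitivity analysis beside a sound primary one. A reader might go further and conclude that the primary result will be invalid or that the expected effect is an artefact of dropout. The documents support neither conclusion.

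**What to change.** In both {20a} and {20c}:

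- Delete the condition on the sensitivity analysis.
- State that the primary maximum likelihood analysis assumes missing at random with a correctly specified model. In {20c} this replaces the clause about independent, identically distributed data.
- Prespecify a delta-adjusted pattern-mixture (tipping-point) analysis, run whatever the dropout pattern, for the T1-to-T2, T1-to-T3 and T1-to-T4 contrasts. Include the case where dropouts stay at their T1 level, and report the worsening among dropouts at which each conclusion changes.
- Complete-case results may stay as a descriptive supplement.

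If the statistical analysis plan already contains such an analysis, it is enough to correct the two sections and refer to it. The cost is wording and a small amount of extra analysis, with no new data. Trial Status puts completion of the primary measures at January 2027, so the change can be fixed before the final data are in.
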